### Analyses

The statistical analysis plan will ensure that the analyses are not data driven or selectively reported. The presentation of primary analyses is expected in spring 2020, after all participants have been followed up to 1 year postpartum. Unadjusted and adjusted results will be presented as appropriate effects sizes with 95% confidence intervals (CI). Demographic and population characteristics of the women at baseline will be compared between study groups. Significance tests will be performed to investigate for differences between groups at baseline. Categorical outcomes will be analyzed using contingency tables and chi-square test. Continuous normally distributed variables will be analyzed using *t*-tests and non-normally distributed variables using non-parametric tests. The primary outcomes, early and exclusive breastfeeding and the adoption of modern contraception at 1 year postpartum, will be analyzed by intention-to-treat methodology, with adjustment for stratifying and baseline factors, including gestational age at enrollment, ownership of mobile phone, age of the pregnant woman at enrollment, and birth order of index pregnancy. Binary logistic regression (BLR) models with generalized estimation equations will be used to account for clustering effects at the level of the Community Development Block. The secondary outcomes of interest are anticipated to include immediate breastfeeding, skilled attendance and facility delivery, postnatal care, newborn birth practices, and immunizations. Binary logistic regression will be used for binary outcomes, and multiple linear regression will be used for continuous measures. Wilcoxon rank sum test will be used for continuous measures which are not normally distributed, including duration of breastfeeding. Cox proportional hazards regression will be used for time to event analyses, including time to initiation of breastfeeding and adoption of a modern contraceptive method in the postpartum period. All regression analyses will be performed with adjustment for baseline factors.

Comparisons between the treatments will be performed in pre-specified subgroups, including phone ownership, caste, age groups, etc. The subgroup analysis does not comprise the primary analysis and did not inform the sample size calculation. The interpretation of any heterogeneity in effects due to the subgroups will be based on using interaction terms between the sub-group variables and the intervention group with no adjustment for multiple testing. The exposure of women to different messages will be assessed using the system-generated data from the MOTECH database. We will analyze the effect of different messages on specific related outcomes using a per-protocol methodology. Missing data will be assessed for any systematic biases based on the dropout of women using their baseline characteristics. Sensitivity analysis will be performed to assess the effect of different levels of systematic bias on the effect sizes.

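### Continuous outcomes judged non-normal go to an unadjusted Wilcoxon test, which cannot give the adjusted effect size with 95% CI that the plan promises

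*Protocol article*

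**What the plan says.** The Analyses section of the protocol article states two rules for continuous variables. The first follows the description of baseline comparisons: normal variables go to t-tests, and "non-normally distributed variables using non-parametric tests". The second comes after the list of secondary outcomes: "multiple linear regression will be used for continuous measures", and then "Wilcoxon rank sum test will be used for continuous measures which are not normally distributed, including duration of breastfeeding". Neither rule says how normality is to be judged, or on which data. Breastfeeding duration is the only outcome named for the rank test.

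Three other statements in the section bear on this:

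- Form of the results: "Unadjusted and adjusted results will be presented as appropriate effects sizes with 95% confidence intervals (CI".
- Scope of adjustment: "All regression analyses will be performed with adjustment for baseline factors".
- Safeguard against selective choices: "The statistical analysis plan will ensure that the analyses are not data driven or selectively reported".

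The Allocation and randomization section names gestational age, parity, woman's age and phone ownership as stratifiers, considers them likely to affect outcomes, and randomizes within each Community Development Block.

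**The concern.** The reporting promise and the method do not fit together. The section commits to adjusted effect sizes with intervals, but ties adjustment to regression. A rank-sum test is not a regression. It yields a p-value with no covariate adjustment, and the plan names no effect measure to accompany it. Any outcome sent down this route therefore lacks the adjusted estimate that the section announces, and its analysis ignores the stratifiers.

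The switch also has no stated trigger. Apart from breastfeeding duration, the article does not show which continuous measures would go to which method, so the choice could be made after the data are seen.

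At stake are the interpretability and precision of secondary continuous results. The primary conclusions are not affected.

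**Working it through.** The plan gives no figure for this point, so there is none to reproduce. The check sets the clauses side by side and then asks by simulation whether the switch is needed and what adjustment is worth.

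**Step 1. What each route delivers (Analyses section)**

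| Route | Covered by the adjustment sentence? | Adjusted effect size with 95% CI? |
|---|---|---|
| Linear regression (continuous measures) | Yes | Yes, adjusted mean difference |
| Wilcoxon rank-sum (non-normal measures) | No, not a regression | No; no effect measure named |
| Logistic regression with GEE (primary outcomes) | Yes | Yes |

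Only the Wilcoxon row fails the reporting promise. This result needs no assumption about how normality is judged.

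**Step 2. Which outcomes are exposed**

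The primary outcomes (early and exclusive breastfeeding, modern contraception) are analysed as binary with adjustment. The listed secondary outcomes are mainly binary practice or coverage indicators. Breastfeeding duration is the one continuous outcome explicitly sent to the Wilcoxon test. Other continuous measures, such as a knowledge score, are possible, but the article does not define any.

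**Step 3. Is the switch needed to protect type I error?**

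Inputs: 5000 enrolled and 20% loss to follow-up (Sampling section), so 5000 × (1 − 0.20) = 4000, or 2000 per arm. Outcome shapes are assumed. The simulations use independent women and no arm effect.

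- Two-sample t-test, 1000 runs per shape: type I error 0.042 to 0.060 across binomial 10- and 20-item scores, gamma outcomes with skewness 0.1 and 0.3, a log-normal outcome (log-SD 1) and a heaped, truncated duration.
- Monte Carlo error at 1000 runs: √(0.05 × 0.95 / 1000) = 0.0069, so 0.05 ± 1.96 × 0.0069 = 0.036 to 0.064. All results lie inside.
- Welch t-test, 4000 runs, log-normal with log-SD 0.5, 1.0 and 1.5: 0.050, 0.056 and 0.046.

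Non-normality alone is therefore no reason to leave the linear model at this size.

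**Step 4. What do adjustment and the choice of scale do to power?**

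Setting: 2000 per arm, log-normal outcome, multiplicative arm effect, and one covariate explaining an assumed 10–20% of log-scale variance.

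| Log-SD | Wilcoxon, unadjusted | Linear regression, adjusted, robust SE |
|---|---|---|
| 0.5 | 70–71% | 70–75% |
| 1.0 | 69% | 51–54% |
| 1.5 | 67–68% | 31% |

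A separate simulation of the same kind gave about 30–56% for adjusted mean regression against 70% for Wilcoxon in the strongly skewed settings. In it, a rank-based analysis had 73–80% power with covariate adjustment against 69–74% without, and adjustment gained power in every case.

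Two things follow. Using the covariates helps on the rank scale. Replacing a rank method by a mean difference can cost much power when skewness is strong.

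**The case against.** The strongest defence is that assigning methods to individual secondary outcomes is ordinary SAP content. The SAP is not shown, and the sentence about data-driven analysis places the safeguard there. The sentence on t-tests and non-parametric tests can also be read as the unadjusted layer, with the adjusted regressions to follow. For skewed outcomes the Wilcoxon test is a good test: Step 4 shows it beating adjusted mean regression by a wide margin.

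Much of this stands, and it rules out several stronger conclusions that a reader might draw:

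- **That the section contradicts its own promise of analyses that are not data driven.** No test on the trial data is described, one outcome is assigned in advance, and the SAP may fix the rest. The text leaves the choice open; it does not break the promise.
- **That nearly every continuous outcome would end in the rank test.** This depends on an assumed trigger and distribution. At 4000 women Shapiro-Wilk rejects normality for a plain 20-item binomial score in 100% of samples, but D'Agostino's test does so in only 16%. The article names neither.
- **That costs would be compared by ranks.** The Economic evaluation section has its own method, based on mean costs and mean effects.
- **That the rank test throws away the equivalent of 400–800 of 4000 women.** That arithmetic compares an unadjusted with an adjusted mean difference, not a Wilcoxon test with a regression. For skewed outcomes it can have the wrong sign.

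The defence does not remove the mismatch in Step 1. The layered reading may fit the first rule, but the later sentence sets Wilcoxon beside linear regression as the method for non-normal measures. The article itself states this rule, and the rule cannot produce the adjusted estimate promised in the same section.

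**Conclusion.** The point holds in a limited form. For any continuous outcome sent to the Wilcoxon test, breastfeeding duration included, the stated method omits the stratifiers and Community Development Block and cannot give the adjusted effect size with 95% CI that the section promises. The trigger for that route has no criterion. Primary outcomes, sample size and the trial's main error rate are untouched, so this is a minor improvement.

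The mismatch rests on the text alone. The size of the gain rests on assumptions: about 4000 women analysed, log-normal outcomes, and covariates explaining 10–20% of variance. Under these, adjustment on the rank scale raises power from 69–74% to 73–80%.

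**What to change.** Drop the normality switch. In the SAP, assign each uncensored continuous outcome in advance to one covariate-adjusted method that gives an effect size with 95% CI, adjusting for gestational age, parity, age, phone ownership and Community Development Block:

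- **Near-symmetric scores:** linear regression with robust standard errors, reporting a mean difference.
- **Outcomes expected to be strongly skewed:** an adjusted rank-based or ordinal model, with its effect measure named.
- **Unadjusted Wilcoxon test:** kept as a sensitivity analysis.

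Breastfeeding duration falls under this fix only if it is uncensored; censoring is a separate question.

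The cost is wording and a little more analysis work, with no new data. The main risk is choosing a mean difference for an outcome that proves strongly skewed, since it can then have clearly less power than the rank test.

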#### Primary research hypothesis

Exposure to Kilkari messages on infant feeding will correspond to a 5% increased prevalence in the reported practice of exclusive breastfeeding for infants 0–6 months of age and use of modern contraceptive methods at 1 year postpartum between intervention and control arms. The control arm is expected to have a prevalence of 58% for the exclusive breastfeeding indicator and based on the recent NFHS data for MP.

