### Sampling

Table 2 summarizes the sample size requirements by activity, along with underpinning assumptions. To determine changes in RMNCH knowledge, practices, and careseeking over time (study aim 1), sampling will be powered to detect changes in coverage across study arms. To detect a 5% difference in reported practice of exclusive breastfeeding assuming an alpha of 0.05, 80% power, the estimated sample size for a two-sample proportions test would be 3200 women. After adjusting for a design effect (variance inflation factor) of 1.25 due to clustering at the level of the Community Development Block and a 20% loss to follow-up from enrollment to endline surveys and a potential loss of 35% of women due to poor reporting of phone numbers and/or changes to original phone numbers provided, a total of 5000 women will be enrolled to the study. Assuming 40% of women have access to a mobile phone, we anticipate that nearly 700,000 households will be listed in all four districts of MP.

**Table 2 Tab2:** Sample size estimates by study aim

Study aim	Survey	Target population	Sample size	Assumptions
Study aim 1a*	Face to face survey to measure changes in infant feeding practices	Women 5–7 months pregnant in four districts of MP	5000	• 5% change in reported practice of immediate and exclusive breastfeeding • Loss to follow-up of 20% from enrolment to final follow-up visit • Variance inflation factor of 1.25
Study aim 1b	Phone survey to measure changes in infant feeding	Postpartum women randomized to Kilkari	5000	Descriptive survey; administered to all women enrolled into the study
Study aim 1c*	Test-retest	Women 5–7 months pregnant in four districts of MP	168 women to be interviewed twice	• Proportion of positive responses of 0.35 for rater 1 and 0.40 for rater 2 • Adjusting for a 15% loss to follow-up/refusal between the first and second surveys
Study aim 1*	Phone survey for postpartum women: infant feeding, essential newborn care, RMC during childbirth	Women 1–4 months postpartum in two districts of MP	880 women interviewed as part of face to face surveys contacted to yield 146 completed face to face and phone survey interviews	• 20% phone survey response rate • Proportion of positive responses of 0.35 for rater 1 and 0.40 for rater 2

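### The primary outcomes are listed inconsistently, and the sample size makes no allowance for testing more than one of them

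*Protocol article*

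**What the plan says.** Two places in the protocol article label outcomes as primary and agree with each other. The Analyses section says "The primary outcomes, early and exclusive breastfeeding and the adoption of modern contraception at 1 year postpartum, will be analyzed by intention-to-treat methodology". The Methods paragraph of the abstract names the same three, introduced as examples rather than as a closed list.

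The section Primary research hypothesis is narrower. It expects a 5% increase in "reported practice of exclusive breastfeeding for infants 0–6 months of age and use of modern contraceptive methods at 1 year postpartum". Early breastfeeding does not appear there.

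The sizing rests on different combinations. The Sampling text reads "To detect a 5% difference in reported practice of exclusive breastfeeding assuming an alpha of 0.05, 80% power", and continues that "the estimated sample size for a two-sample proportions test would be 3200 women". In the same section, the Table 2 row for study aim 1a assumes a "5% change in reported practice of immediate and exclusive breastfeeding". Yet the Analyses section says "The secondary outcomes of interest are anticipated to include immediate breastfeeding", and the Measurement section lists immediate and early breastfeeding as separate survey items.

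The one planning rate labelled as a control-arm expectation is for exclusive breastfeeding: "The control arm is expected to have a prevalence of 58% for the exclusive breastfeeding indicator". No rate is given for modern contraception.

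**The concern.** A reader cannot tell from the article whether the trial has two or three primary outcomes, or whether breastfeeding initiation is primary, secondary or both. Until that is settled, it is open which result would support a claim that Kilkari works. The sizing uses the whole 0.05 on one outcome. If several outcomes can each support a primary claim at that level, the error rate for the overall claim exceeds the level behind the sample size. If instead every outcome must succeed, the error is controlled, but the power is no longer the planned 80%.

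**Working it through.** **1. The places side by side**

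| Place | Early initiation | Immediate initiation | Exclusive breastfeeding | Modern contraception |
|---|---|---|---|---|
| Abstract, Methods | primary | – | primary | primary |
| Primary research hypothesis | – | – | named | named |
| Sampling, text | – | – | sized | – |
| Sampling, Table 2, aim 1a | – | sizing assumption | sizing assumption | – |
| Analyses | primary | secondary | primary | primary |

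If early and immediate mean the same thing, Analyses makes one outcome both primary and secondary. If they differ, as the Measurement section implies, the Table 2 row rests partly on a secondary outcome, and early breastfeeding is primary but appears in neither the hypothesis nor the sizing. Both readings need a correction.

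**2. The plan's own figure**

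Inputs: 58% in control (Primary research hypothesis), a 5-point difference, alpha 0.05 and 80% power (Sampling), and about 1:1 allocation (Allocation and randomization). Sidedness is not stated. I assume two-sided, since results are to be reported with 95% confidence intervals.

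n per arm = [z(1−α/2)·√(2p̄q̄) + z(0.80)·√(p₁q₁ + p₂q₂)]² / d², where p̄ = 0.605 and q̄ = 1 − p̄.

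- √(2 × 0.605 × 0.395) = 0.6913
- √(0.58 × 0.42 + 0.63 × 0.37) = 0.6904
- (1.960 × 0.6913 + 0.842 × 0.6904)² / 0.05² gives 1500 per arm, **3000 in total**, or 3080 with continuity correction

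The stated 3200 is therefore not reproduced exactly; it is somewhat conservative. Rates of 50% versus 55% come close, at 3130 (3210 with continuity correction).

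**3. Is there a multiplicity allowance in 3200?**

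The same formula with alpha divided equally gives:

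- α/2 = 0.025 (z = 2.241): 1816 per arm, 3632 in total
- α/3 = 0.0167 (z = 2.394): 2001 per arm, 4002 in total

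Neither gives 3200. After the design effect of 1.25 and 20% loss, they would mean enrolling 3632 × 1.25 / 0.80 = 5675 or 4002 × 1.25 / 0.80 = 6254 women, against 3200 × 1.25 / 0.80 = 5000 as planned.

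**4. Family-wise error if each outcome is tested at 0.05 and any one counts**

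- Two independent outcomes: 1 − 0.95² = 9.75%
- Three independent outcomes: 1 − 0.95³ = 14.26%
- Bounds under any dependence: 10% and 15%
- Three equally correlated test statistics (simulated): 13.6% at r = 0.3, 12.6% at r = 0.5, 9.8% at r = 0.8
- Two: 9.5%, 9.1% and 7.8% at the same correlations

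**5. Power under the possible rules**

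Effective N = 5000 × 0.80 / 1.25 = 3200, that is 1600 per arm. Power for 58% versus 63% = Φ[(0.05·√1600 − z(1−α/2) × 0.6913) / 0.6904]:

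- α = 0.05: 82.5%
- α = 0.025: 74.3%
- α = 0.0167: 69.1%

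If all outcomes must succeed, and for illustration each has 82.5% power independently, joint power is 0.825² = 68% for two and 0.825³ = 56% for three.

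**The case against.** The strongest objection is that no error rate can be read off this document. The article gives no rule for declaring success. Its one remark about not adjusting for multiple testing concerns subgroup interactions. It also refers to a statistical analysis plan, where a hierarchy or alpha split would commonly be set out. This stands. A reader might infer that the plan as written carries a false-positive risk of 14%. That figure needs three outcomes, each tested at 0.05, any one counting, no adjustment and independence. The success rule and the absence of adjustment are nowhere stated, and if all outcomes had to succeed the error would be at or below 5%.

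A reader might also count three conflicting primary lists. Only two differing lists serve as primary: the one shared by the abstract and Analyses, and the one in the hypothesis. The Table 2 entry is a sizing assumption for an infant-feeding survey, where contraception would not be expected.

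Nor does sizing on exclusive breastfeeding alone leave the other outcomes underpowered at 0.05. A 5-point difference needs most women at 47.5% versus 52.5%, where the total is 3138, still below 3200. For 35% versus 40% (the setting section gives 35% breastfed within one hour) it is 2942.

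What the objection does not remove is the contradiction itself. A multiplicity rule in the analysis plan cannot settle which of the protocol's lists it applies to.

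**Conclusion.** The point holds as an inconsistency that must be reconciled, with a conditional consequence for error control. The protocol gives two different primary lists, a sizing row that matches neither, and unclear naming of breastfeeding initiation. The sizing spends the full 0.05 on exclusive breastfeeding and contains no allowance for further primary tests.

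If two or three outcomes are each tested at 0.05 unadjusted and any one suffices, the family-wise error is about 10% or 14% under independence, and lower with positive correlation, which is plausible for two breastfeeding outcomes. The document does not establish that this rule will be used. The sample-size and power figures assume two-sided tests and 58% versus 63%. The power figures also assume an effective N of 3200, which reflects only the design effect and the 20% loss. The Sampling section also mentions a 35% loss through phone numbers, which 5000 does not absorb; if it occurred in full, power would be lower throughout.

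**What to change.** Use one primary list in the abstract, Primary research hypothesis, Sampling (text and Table 2) and Analyses. Use one name and definition for breastfeeding initiation, or state how early and immediate differ. Then state a success rule consistent with the 0.05 used for sizing. The document does not dictate which rule; the options are:

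- **Fixed sequence starting with exclusive breastfeeding at two-sided 0.05.** Its power is unchanged and no extra women are needed. The downside is that later outcomes, including contraception, are confirmatory only if exclusive breastfeeding succeeds.
- **Holm or Hochberg across the primary outcomes.** Each can then support a claim on its own. Power must be restated; a full Bonferroni split, the conservative case, gives about 74% for two outcomes and 69% for three.
- **All outcomes required.** No alpha split is needed, but joint power must be stated, and that needs a planning rate for contraception.

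Moving early initiation to secondary would shorten the list, but it overrides the abstract and Analyses, so it is the investigators' choice. The cost of the first option is wording in the protocol and analysis plan, plus a check that the registry entry agrees. The choice should be dated before outcome data by arm are seen.

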### Measurement

Figure 2 provides an overview of enrolment and study design over time and the Standard Protocol Items: Recommendations for Interventional Trials (SPIRIT) are presented in Fig. 3 and Additional file 1. At enrollment, women will be administered a survey containing modules on phone ownership, geographical and demographic characteristics, knowledge (danger signs during pregnancy, delivery, and postpartum; essential newborn care; nutrition; hygiene, diarrhea treatment, family planning, etc.), practices (immediate, early, and exclusive breastfeeding; complementary feeding; skin-to-skin care, etc.), RMC, and coverage for antenatal care, delivery, and postnatal care. Around 6–8 weeks after the expected date of delivery, a phone survey will be administered to a random sample of the enrolled women until a target sample size of 3500 is attained (1750 each in intervention and control arms) to assess breastfeeding and newborn care practices. An endline survey will be carried out from November 2019 to February 2020 and each woman will be followed up at 12 months postpartum based on their expected date of delivery at enrollment. The endline survey will capture data on practices during pregnancy and intrapartum and postpartum periods.

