#### Study aim 1: Generate evidence on the effectiveness of Kilkari in four districts of MP

Knowledge attitudes and practices (KAP) surveys will be administered at baseline and endline containing modules on phone ownership, geographical and demographic characteristics, knowledge (danger signs during pregnancy, delivery, and postpartum; essential newborn care; nutrition; hygiene, diarrhea treatment, family planning, etc.), practices (immediate, early, and exclusive breastfeeding; complementary feeding; skin-to-skin care, etc.), RMC, and coverage for antenatal care, delivery, and postnatal care. Questions on exposure to and sources for health information content will additionally be asked to identify possible sources of contamination. The list of individuals randomized to receive Kilkari content will be provided to BBC Media Action for enrollment into Kilkari continuously throughout the implementation of the baseline survey. Following 11–12 months, participants from both study arms will be interviewed as part of the face to face endline survey.

A phone survey will be administered to all study arm participants on a rolling basis at 1 month postpartum to measure RMNCH practices, including infant feeding practices and essential newborn care as well as RMC. Methods to generate a validated phone survey tool are described elsewhere and in brief will include a face to face survey administered to women during pregnancy and with a live birth outcome in the preceding 1–4 months postpartum at the time of the household listing. A sub-sample of respondents from the initial face to face survey will be administered a second test-retest survey by a separate but similar profile of enumerator. Findings from the face to face surveys will be used to generate phone survey tools which will be implemented amongst a random sample of pregnant and postpartum women who consent to be called for the follow-up phone survey. Analyses to assess the intermodal reliability of face to face versus phone survey responses will be used to generate a validated tool. The tool developed for postpartum women will subsequently be administered to women enrolled into the iRCT during pregnancy at 1–4 months postpartum (Fig. 2).

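### Duration of breastfeeding is assigned to a rank sum test that cannot represent women still breastfeeding at endline; the power lost depends on a share the article does not give

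*Protocol article*

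**What the plan says.** The Analyses section allocates methods by type of outcome. For skewed continuous measures, "Wilcoxon rank sum test will be used for continuous measures which are not normally distributed, including duration of breastfeeding". The next sentence gives event times to a different method: "Cox proportional hazards regression will be used for time to event analyses, including time to initiation of breastfeeding", with postpartum adoption of modern contraception as its other example. Duration of breastfeeding is not among the Cox examples. The same section promises effect sizes with 95% confidence intervals, unadjusted and adjusted, and baseline adjustment in all regressions.

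On when observation stops, the Measurement section says that "each woman will be followed up at 12 months postpartum based on their expected date of delivery at enrollment" and that "An endline survey will be carried out from November 2019 to February 2020". Under Study aim 1 it says "Following 11–12 months, participants from both study arms will be interviewed as part of the face to face endline survey", without giving the date from which those months run.

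The article does not say whether duration means any or exclusive breastfeeding, how a woman still breastfeeding is recorded, or what share is expected to be breastfeeding at endline. Duration is not a primary outcome. It is also absent from the secondary list ("immediate breastfeeding, skilled attendance and facility delivery, postnatal care, newborn birth practices, and immunizations"), although that list is only an anticipated one.

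**The concern.** Duration of breastfeeding runs from birth to stopping. With a single interview near 12 months, a woman who has not stopped contributes only a lower bound, namely her child's age that day. A plain rank sum test takes one number per woman and has no place for a censoring flag. If the child's age at interview is used, two women who are both still breastfeeding are ranked by when they were interviewed. Those ages will differ, because visits are timed from the expected and not the actual delivery date and are spread over a window of months. If such women are left out instead, the analysis selects on the outcome.

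What is at stake is sensitivity: a real difference in stopping could be missed. The plan already has the suitable method in its next sentence and does not apply it to this variable.

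**Working it through.** The article gives no figure for duration (no median, spread, hazard ratio or power), so there is no stated result to reproduce. The check is a simulation with its assumptions shown.

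**Inputs from the article (Sampling).** "a total of 5000 women will be enrolled to the study", with "a 20% loss to follow-up from enrollment to endline surveys". With about equal arms, 5000 × 0.80 / 2 = 2000 women per arm at endline. The further 35% loss that the article attributes to phone numbers is not applied here. Alpha is 0.05, taken as two-sided.

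**Assumptions not in the article.** Exponential stopping times; control share still breastfeeding at 12 months, c, from 10% to 90%; hazard ratio for stopping 1.0 or 0.85; interviews spread uniformly over 1 or 3 months centred on month 12; no clustering; 400 replicates per cell.

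**Step 1: pairs decided by interview timing.** If interview age is entered as the duration, a between-arm pair is ordered by interview timing alone when both women are still breastfeeding. With equal arms that share is c × c: 1% at c = 10%, 9% at 30%, 25% at 50%, 49% at 70%, 64% at 80% and 81% at 90%. It passes one half at c = √0.5 ≈ 71%.

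**Step 2: power at hazard ratio 0.85** (range over the two interview windows). The log-rank test stands in for an unadjusted Cox model.

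| Still breastfeeding (control) | Wilcoxon, interview age entered | Wilcoxon, capped at a common age | Log-rank | Wilcoxon, stopped women only |
|---|---|---|---|---|
| 10% | 0.99 | 0.99 | 1.00 | 0.70–0.71 |
| 30% | 0.98 | 0.97–0.98 | 0.98–0.99 | 0.28–0.29 |
| 50% | 0.89–0.90 | 0.94–0.95 | 0.95–0.96 | 0.10–0.13 |
| 70% | 0.54–0.55 | 0.72–0.73 | 0.76–0.79 | 0.06–0.09 |
| 80% | 0.29 | 0.54 | 0.57–0.58 | 0.05–0.06 |
| 90% | 0.12–0.13 | 0.35 | 0.34–0.38 | 0.05–0.07 |

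**Step 3: check of the log-rank column.** Power ≈ Φ(|ln 0.85| × √(D/4) − 1.96), where D is the number of women who have stopped by month 12.
- At c = 70%, D = 2000 × [(1 − 0.70) + (1 − 0.70^0.85)] = 2000 × (0.300 + 0.2615) = 1123. Then 0.1625 × √280.8 = 2.72, and Φ(0.76) ≈ 0.78.
- At c = 90%, D = 2000 × (0.100 + 0.0857) ≈ 371. Then 0.1625 × √92.8 = 1.57, and Φ(−0.39) ≈ 0.35.

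Both agree with the simulation.

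**Step 4: type I error.** At hazard ratio 1.0 the Wilcoxon test with interview ages entered rejects in 3–7% of replicates across the twelve cells (Monte Carlo standard error √(0.05 × 0.95 / 400) ≈ 1.1 points). There is no inflation.

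**Step 5: other effect sizes.** With interviews at 11–12 months, 600 replicates and assumed shares still breastfeeding of 50% against 55%, 30% against 35%, and 10% against 13%, Wilcoxon power is 82%, 91% and 90%, and log-rank power is 91%, 94% and 95%. At 80% against 84%, repeat runs give 54–55% for Wilcoxon and 87–92% for log-rank. The pattern is the same: the gap is small at low shares and large at high ones.

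**The case against.** The strongest reply is that the loss comes from an assumed way of recording ongoing breastfeeding and not from the rank test itself. Tying all durations at a common age is an ordinary option, and the table shows it recovers most of the loss when interviews fall close together. That coding could properly sit in an analysis plan that is not shown. This stands in part. The article nevertheless fixes the test, and the test as named has no provision for censoring. Capping also works less well if interview ages are wide: with an assumed 7–13 month spread, which the article does not state, capping at 7 months gave 71–74% power against 84–85% for log-rank.

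Second, the term is undefined. The primary hypothesis concerns exclusive breastfeeding at 0–6 months. If exclusive duration is meant, most values would be complete by month 12 and censoring would be slight. This stands and limits the point.

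Third, the outcome is marginal: it appears once, as an example, and no sample size or main conclusion rests on it. This also stands.

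A reader might go further and infer that the comparison would be largely noise from interview timing. That needs more than about 71% still breastfeeding and interview age entered as the duration, and the article establishes neither. A reader might also infer bias between arms or false positives. Interviews are timed by the same rule in both arms, allocation is balanced within Community Development Block, and the simulated type I error is near nominal, so that is not supported. Nor does it follow that reported medians would be interview ages: that needs more than half still breastfeeding, and the article does not commit to reporting medians.

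**Conclusion.** The point holds in a limited form. The article names a test that cannot represent right-censored durations for a variable that a single interview near 12 months will censor in every woman still breastfeeding. If interview age is entered, the consequence is lost power, ranging from negligible at 30% or less still breastfeeding to roughly half or more of the attainable power at 80–90%. Excluding those women costs more at every share examined.

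These sizes rest on the assumed hazard ratio of 0.85, exponential stopping times, 2000 women per arm and interviews within 1 or 3 months around month 12. The share still breastfeeding, which drives the result, is not in the article. At 90% even the log-rank test has little power for this effect, so the change does not guarantee an informative comparison. Under an exclusive-breastfeeding definition the loss is small. The primary outcomes are untouched, and this is a minor improvement.

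**What to change.** Remove duration of breastfeeding from the Wilcoxon sentence. Define it as any or exclusive breastfeeding, or both as separate outcomes. Analyse it as time from birth to cessation, with women still breastfeeding censored at the child's age at the endline interview. Show Kaplan-Meier curves by arm and estimate the effect with the covariate-adjusted Cox regression already planned for the other event times. This also gives an effect size with a confidence interval, as the Analyses section promises, which a rank sum p-value does not. If a rank test is kept as a supporting analysis, state in advance a common age at which all durations are capped.

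The cost is a sentence or two in the analysis plan. No new data are needed, provided the endline survey records whether the woman is still breastfeeding, the age at stopping if not, and the child's age at interview; the article does not list the questions, so this should be confirmed.
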